### Gene Expression Profiling

Primers for the BCAT1, BCKDK, DCAKD, LPL, PANK1, SPTSSA, and PCTP genes will be determined using the web tool provided by Thermo Fisher Scientific. After treatment, the BeWo cells will be gently washed with precooled phosphate-buffered saline. Total RNA will be extracted using the RNeasy mini kit (Qiagen). Quantitative polymerase chain reaction (qPCR) will be performed with a real-time PCR detection system and software (Applied Biosystems).

### Data and Statistical Analysis

The patient metabolite-concentration data will be examined to determine differences between the preeclampsia and healthy patient samples and to determine if they follow normal distributions. If they do, paired and unpaired 2-tailed *t* tests will be carried out to determine if the concentrations are significantly different. If they are not, then the Mann-Whitney *U* test will be used. These same tests will be used for metabolite concentrations in the in vitro cell cultures. A correlation matrix will be calculated between the metabolite concentrations and patient characteristics, including weight, age, and week of gestation, to determine if there are any associations. In addition to the planned targeted analysis to test our hypothesis, the plasma metabolomes will also be measured with untargeted HPLC/MS, and the data will be analyzed using multiple-testing correction-adjusted *t* tests and partial least-squares discriminant analysis to identify which metabolites are altered by preeclampsia status. Pathway enrichment will be used to identify dysregulated pathways, which will then be compared with previously published data.

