**Methods:**

This manuscript provides a rationale and a protocol for a clinical study and laboratory experiments to test the hypothesis. The methods have 3 key aspects. Phase 1 comprises optimization of assays of 5 key metabolites arising from CoA restriction, namely L-leucine, ketoisovalerate, ketodeoxycholate, oleic acid, and sphingosine-1-phosphate. Phase 2 comprises recruitment of patients to obtain serum samples to measure the metabolites, and phase 3 comprises culturing and treating trophoblast cells to induce CoA restriction and test the effects of the metabolites on the cells. Patients with preeclampsia and healthy controls will be recruited based on World Health Organization criteria for preeclampsia. Exclusion criteria include multiple pregnancies, premature rupture of membranes, and various medical complications. Blood samples will be collected and analyzed using high-performance liquid chromatography/mass spectrometry (HPLC/MS) to quantify key metabolites associated with CoA restriction. For trophoblast cell studies, BeWo cells will be cultured under conditions likely to induce CoA restriction, including hypoxia and human chorionic gonadotropin supplementation, and will also be treated with the key metabolites to determine what effect they might have. Cell viability, apoptosis, energy metabolism, and gene expression (focusing on genes involved in CoA synthesis and metabolism) will be assessed. Statistical analysis will involve 2-tailed *t* tests or Mann-Whitney *U* tests to compare metabolite concentrations between patients with preeclampsia and controls. A correlation matrix will be used to explore associations between metabolite levels and patient characteristics.

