### Recruitment

Women with preeclampsia will be identified by the obstetricians collaborating with the study from the antenatal clinics and wards at Latifa Hospital in Dubai. Women with preeclampsia who meet the inclusion criteria outlined below will be approached verbally, asking if they would like to participate in this study. A patient information sheet will be provided, and after they provide written informed consent, they will be recruited into the study.

Baseline clinical and laboratory characteristics will be collected from the patients’ medical notes, including obstetric history, booking weight, height, renal and liver function, comorbidities, and smoking history. A data collection form has been designed for this purpose (Multimedia Appendix 1). The collected data will be anonymized and linked to samples by study ID only. Concurrent control participants will be identified following a review of the antenatal clinic lists to seek women with uncomplicated pregnancies who are undergoing routine antenatal care in the same antenatal clinic at Latifa Hospital in Dubai. Controls will be matched for approximate weight, age (5-year age group) and week of gestation. Control participants who meet the inclusion criteria outlined below will also be approached verbally, asking if they would like to participate in this study.

Patient blood samples will be taken at the time of routine phlebotomy for blood tests required as part of clinical care. As such, no adverse events specifically related to the study procedure are anticipated.

Blood samples will be collected in a heparinized EDTA (ethylenediaminetetraacetic acid) 10-ml container and transported immediately on ice to the laboratory for processing, as described in Blood Metabolite Analysis section below. One member of the research team has the responsibility for sample processing to ensure consistency. Metabolite measurements will be conducted by 2 members of the research team.

Preeclampsia will be defined as per the WHO Recommendations for Prevention and Treatment of Pre-eclampsia and Eclampsia [18]; specifically, the onset of a new episode of hypertension during pregnancy, characterized by persistent hypertension (diastolic blood pressure ≥90 mm Hg), and substantial proteinuria (>0.3 g/24 hours or more or a protein level of +2 or above in the urine dipstick test). The gestational week in which the sample is collected will be recorded for all women.

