### Power

This prospective, cross-sectional, case-control study will include 40 pregnant women, with 20 women diagnosed with, followed up on, and treated for preeclampsia at Latifa Hospital in Dubai, and 20 women (matched for approximate weight, age [5-year age group], type of pregnancy [single or multiple], and week of gestation) with normal pregnancies. This is about half the numbers in previous metabolomic studies of preeclampsia but should be sufficient to produce the variability required given that matched controls are involved. If not, this pilot study will provide the data to carry out a sample-size calculation for a future larger clinical study. The analysis of data from this study will be primarily focused on descriptive statistics and estimates of precision to inform a planned larger validation study. The proposed sample size in our study is also consistent with the findings from a study on the target sample sizes set for pilot and feasibility randomized controlled trials in the United Kingdom [28].

For the HPLC/MS metabolite measurement, assuming a coefficient of variance of 30%, which corresponds to several multiples of observed technical variation, power calculations indicate this study will be 80% powered to detect changes of 27%. The minimum detectable effect size was calculated using G*Power [29,30].

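### Matched controls are analysed by paired and unpaired t tests with neither named as deciding, and the only non-normal fallback, Mann-Whitney U, ignores the matching

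*Protocol article*

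**What the plan says.** The Recruitment section sets up the matching: "Controls will be matched for approximate weight, age (5-year age group) and week of gestation". The Power section repeats it for a study that "will include 40 pregnant women, with 20 women diagnosed with, followed up on, and treated for preeclampsia at Latifa Hospital in Dubai, and 20 women" with normal pregnancies. It concedes that this is about half the size of earlier metabolomic studies, and argues that the number "should be sufficient to produce the variability required given that matched controls are involved".

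The Data and Statistical Analysis section gives the test rule for the targeted metabolites. Normality is examined first. For normal data: "If they do, paired and unpaired 2-tailed *t* tests will be carried out to determine if the concentrations are significantly different". Otherwise: "If they are not, then the Mann-Whitney *U* test will be used". No rank test for pairs is named, and neither t test is called primary.

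The abstract does not settle the choice: "Statistical analysis will involve 2-tailed *t* tests or Mann-Whitney *U* tests to compare metabolite concentrations between patients with preeclampsia and controls".

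The Power section also says that the analysis will be mainly descriptive and aimed at estimates of precision for a larger validation study.

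**The concern.** The matching is offered as the reason why a small sample is enough, yet the analysis makes use of it optional for normal data and impossible for non-normal data.

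Two things follow. First, a metabolite can be significant by one t test and not by the other, and the protocol gives no rule for which result is the study's answer. Second, a metabolite that fails the normality check moves to a test whose standard error takes no account of pairing. If matching has made case and control concentrations alike within pairs, that test is too cautious and discards precision that the design paid for. The same applies to any unpaired confidence interval carried forward to plan the larger study.

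**Working it through.** **Inputs.** From the Power section: 20 cases and 20 controls, CV 30%, detectable change 27%, power 80%. From Data and Statistical Analysis: two-sided tests. Assumed, because the protocol does not give them: alpha 0.05, one-to-one pairs, and a within-pair correlation ρ of 0 to 0.7.

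**Step 1: the plan's own figure.** Standardised effect d = 27/30 = 0.90. For the unpaired t test the noncentrality is d × √(n/2) = 0.90 × √10 = 2.85 on 38 df (critical value 2.02). Power is 0.792, and 80% power is reached at 27.3%. The stated 27% therefore reproduces as an unpaired calculation and takes no credit for matching.

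**Step 2: the paired t test on the same inputs.** SD of the within-pair difference = 30% × √(2(1 − ρ)). Noncentrality = 27/SD × √20 on 19 df (critical value 2.09).

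| ρ | SD of difference | Noncentrality | Power at 27% | 80%-power change |
|---|---|---|---|---|
| 0 | 42.4% | 2.85 | 0.770 | 28.0% |
| 0.3 | 35.5% | 3.40 | 0.897 | 23.4% |
| 0.5 | 30.0% | 4.02 | 0.968 | 19.8% |

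**Step 3: why unpaired tests are conservative.** The unpaired standard error of the mean difference is 30% × √(2/20) = 9.5%, whatever ρ is. The true value is 9.5% × √(1 − ρ): 7.9% at ρ = 0.3 and 6.7% at ρ = 0.5.

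**Step 4: simulation.** Normal data, 20 pairs, with no difference and with d = 0.90. There were 40,000 data sets per setting for the t tests and Mann-Whitney. The signed-rank test was run on between 4,000 and 40,000; the small spread at ρ = 0.3 comes from different runs.

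| | ρ = 0 | ρ = 0.3 | ρ = 0.5 |
|---|---|---|---|
| Mann-Whitney, type I error | 5.0% | 2.0% | 0.8% |
| Mann-Whitney, power | 77% | 81% | 84% |
| Signed-rank, power | 74–75% | 87–89% | 96% |
| Unpaired t, power | 79% | 83% | 87% |
| Paired t, power | 77% | 90% | 97% |
| Either t test significant, type I error | 6.1% | 5.2% | 4.8% |
| The two t tests disagree at a true 27% change | 5.7% | 7.4% | 9.8% |

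At ρ = 0.7 the t tests disagree in 8.5% of data sets, and Mann-Whitney has 0.1% type I error with 89% power against more than 99% for signed-rank.

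**Reading.** At ρ = 0 the paired tests lose about 2 points of power. At ρ = 0.3 to 0.5 the Mann-Whitney fallback gives up about 6 to 12 points against the signed-rank test.

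**The case against.** The strongest reply has four parts.

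*The pilot is mainly descriptive.* The protocol says so, and its Limitations section expects at least trends and otherwise data for a later power calculation. This stands and lowers the severity. It does not remove the point: the same section has the tests decide whether concentrations differ significantly, and calls the targeted analysis the one that tests the hypothesis. Estimates of precision also depend on whether the pairs are respected.

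*One-to-one pairing is not stated.* True. Approximate weight, a 5-year age band and gestational week could be frequency matching, under which unpaired tests are ordinary. But a paired t test needs defined pairs. If there are none, that test cannot be run, so the section needs changing either way.

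*Every correlation is assumed.* This also stands. Loose matching may give little correlation, and at zero the Mann-Whitney test loses nothing.

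*A fuller analysis plan may name the deciding test.* Possible, but the protocol itself fixes the fallback, and that fallback ignores pairs.

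A reader might infer more than the text supports. The protocol does not say that the smaller of two p-values will be quoted, and even if it were, type I error would reach only about 6%, and about 5% once matching works. It does not promise a fold change or a paired SD, and running Mann-Whitney does not stop anyone from computing descriptive estimates. It names no normality test, so figures for how often such a check would misfire rest on the reader's own choices.

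**Conclusion.** The point holds at moderate severity. The protocol states a test rule that leaves the deciding t test open and, for non-normal data, names a test for independent groups in a design defended by its matching.

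The consequence is lost power and over-cautious inference, not false positives. At the protocol's own effect the loss in the fallback is about 6–8 points at a within-pair correlation of 0.3 and 12 points at 0.5. In the normal branch the two planned t tests would give conflicting answers in roughly 6–10% of data sets at a true 27% change.

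These sizes assume one-to-one pairs, positive correlation, alpha 0.05 and normal data. The direction needs only the first two; with no correlation, nothing is lost by the unpaired tests. The stated 27% is not wrong: it is correct for an unpaired comparison.

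**What to change.** In Data and Statistical Analysis:

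- State whether controls are individually matched.
- If they are, name the paired t test as the primary targeted comparison. Check normality on the within-pair differences, using the log scale if they are skewed.
- Replace Mann-Whitney with the Wilcoxon signed-rank test as the fallback.
- Report the paired difference or ratio with its 95% confidence interval.
- Label any unpaired test a sensitivity analysis.
- Keep the link between each case and her control in the data set.
- If controls are only frequency-matched, drop the paired test and adjust the group comparison for weight, age and gestational week.

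The cost is a few sentences and one pair identifier, with no extra women or assays. The Results section says data analysis has not begun, so the choice can still be made before any comparison is seen. The downside is about 2 points of power if matching proves uninformative.

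### The metabolite-by-characteristic correlation matrix should be adjusted for case/control status; if pooled, it weakens correlations with the matched characteristics and can create them for disease-affected ones

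*Protocol article*

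**What the plan says.** The analysis section of the protocol article plans one exploratory correlation analysis: "A correlation matrix will be calculated between the metabolite concentrations and patient characteristics, including weight, age, and week of gestation". The abstract gives its purpose: "A correlation matrix will be used to explore associations between metabolite levels and patient characteristics". Neither place says whether cases and controls are pooled, analysed separately or adjusted for group. In the same paragraph, case status does define the *t* tests and the discriminant analysis.

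The sample is fixed by outcome. The Power section says the study "will include 40 pregnant women, with 20 women diagnosed with, followed up on, and treated for preeclampsia", with 20 women with normal pregnancies as controls. Under Recruitment, "Controls will be matched for approximate weight, age (5-year age group) and week of gestation". The Power section adds type of pregnancy as a fourth matching factor, but multiple pregnancy is an exclusion criterion, so that factor does not vary.

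The three characteristics named for the matrix are therefore all matching factors. The list is open-ended, however, and the baseline data to be collected are wider, "including obstetric history, booking weight, height, renal and liver function, comorbidities, and smoking history". Renal and liver function are not matched, and the Background says that severe disease damages both organs.

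**The concern.** In a sample built from two outcome groups, a correlation over all women has two parts: the association among women of the same status, and the component produced by the two groups having different means. Only the first answers whether a metabolite goes with a patient characteristic.

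The second part acts in two ways. If the characteristic is balanced by matching, the metabolite shift adds variance that the characteristic cannot explain, and the coefficient shrinks. If the characteristic also differs between cases and controls, the two shifts produce a correlation of their own.

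The effect grows with the metabolite difference. The Discussion expects the chosen metabolites to be strongly raised in cases, so the better the main hypothesis does, the harder a pooled matrix is to interpret.

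**Working it through.** **Inputs from the protocol article.** There are 20 cases and 20 controls (Power). The CV is 30% ("assuming a coefficient of variance of 30", in per cent). The detectable change is 27% ("power calculations indicate this study will be 80% powered to detect changes of 27", in per cent). In SD units this is 27/30 = 0.9.

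**Assumptions.** The documents give no value for the following, so ranges are used: metabolite shifts above 0.9 SD, shifts in a characteristic, within-group correlations, and a two-sided 0.05 level.

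**The plan's own figure.** An unpaired two-sided *t* test with 20 per group has 80% power at a change of 27.3%, and 79.2% power at exactly 0.9 SD. The stated 27% reproduces. Here it only supplies the 0.9 SD shift.

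**Formula.** With equal groups, let *r*w be the within-group correlation, and let *dm* and *dx* be the case-control differences in metabolite and characteristic, in within-group SDs. Then

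pooled *r* = (*r*w + *dm*·*dx*/4) / √[(1 + *dm*²/4)(1 + *dx*²/4)].

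**Matched characteristic (*dx* = 0).** The formula reduces to *r*w / √(1 + *dm*²/4).

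- With *r*w = 0, pooled *r* = 0. In 20,000 simulated studies the rejection rate was 4.9%, and 3.4% with close pair matching. No false association arises.
- *dm* = 0.9: 1/√1.2025 = 0.912, attenuation of about 9%.
- *dm* = 1.5: 1/√1.5625 = 0.80, attenuation of 20%.
- *dm* = 2: 1/√2 = 0.707, attenuation of about 29%.
- A true *r*w of 0.45 becomes 0.41, 0.36 and 0.32 at these shifts. Power falls from about 84% to about 77%, 64% and 52%.
- Matching is only approximate. A residual difference of 0.2 SD with *dm* = 0.9 gives 0.045/√(1.2025 × 1.01) = 0.04, which is negligible.

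**Unmatched, disease-affected characteristic (*r*w = 0, *dm* = 0.9).**

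- *dx* = 1: 0.225/√(1.2025 × 1.25) = 0.18.
- *dx* = 1.5: 0.3375/√(1.2025 × 1.5625) = 0.25.
- *dx* = 2: 0.45/√(1.2025 × 2) = 0.29.
- The critical |*r*| for 40 women is 0.312. In simulation the pooled coefficient passes it in about 21%, 35% and 47% of studies.

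**Adjusted for case status.** Centring within groups leaves 40 − 2 − 1 = 37 df. In simulation, with *r*w = 0, rejection was 4.7% to 5.4% in every scenario. With *r*w = 0.5, the mean coefficient stayed at about 0.49 and power at about 92%, whatever the metabolite shift. The pooled matrix had power of 86%, 73% and 61% at shifts of 0.9, 1.5 and 2 SD.

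**The case against.** The strongest reply is that pooling is inferred from silence. A condensed article need not say how an exploratory matrix is stratified, and the team may already intend a within-group analysis. It is true that the text does not state pooling. But a single matrix is planned in a paragraph on the data of both groups, and the other analyses there use case status explicitly, so pooling is what a reader following the text would do.

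Three further objections stand and limit the point.

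- A reader might infer that the matrix will produce false associations with weight, age or gestation. It will not: they are matched. False associations need an added, unmatched characteristic. Renal and liver function are collected, but the plan does not commit to putting them in the matrix, and the size of their case-control difference is assumed.
- A reader might infer that real associations with the matched characteristics will be hidden. At the protocol's own 0.9 SD they are only weakened, by about 9%, with a power loss of about 7 points. Larger losses need shifts that the Discussion's expectation would allow but does not quantify.
- A reader might infer that the matrix will guide covariate choice in the later study. The article does not say so. It speaks of descriptive statistics, precision and a sample-size calculation.

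Finally, the plan sets no significance rule for the matrix, so the rejection rates above illustrate the distortion rather than measure an error rate of the plan.

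**Conclusion.** The point holds as an inexpensive improvement to an exploratory analysis, not as a major error. As naturally read, the matrix cannot separate association with a characteristic from association with being a case. For the three named characteristics the consequence is attenuation: about 9% at the protocol's 0.9 SD, and about 20% to 29% if the shift is 1.5 to 2 SD. For an added, disease-affected characteristic the consequence is a spurious pooled *r* of about 0.18 to 0.29, for assumed characteristic shifts of 1 to 2 SD at a 0.9 SD metabolite shift.

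Both results depend on the matrix being pooled. The case-control comparison of metabolite concentrations, which tests the hypothesis, does not use the matrix and is unaffected.

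**What to change.** In Data and Statistical Analysis, state that correlations between metabolites and patient characteristics will be adjusted for case/control status (partial correlation given group, 37 df). Show the case-only and control-only coefficients beside them as description only: with 20 women each they are imprecise (critical |*r*| about 0.44 per group). Log transformation is optional and not part of this change.

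The cost is one sentence and one degree of freedom, with no new data. The Results section reports that data analysis has not begun, so the sentence can still be added beforehand. If a within-group analysis is already intended, the sentence simply makes that clear.

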### Power

This prospective, cross-sectional, case-control study will include 40 pregnant women, with 20 women diagnosed with, followed up on, and treated for preeclampsia at Latifa Hospital in Dubai, and 20 women (matched for approximate weight, age [5-year age group], type of pregnancy [single or multiple], and week of gestation) with normal pregnancies. This is about half the numbers in previous metabolomic studies of preeclampsia but should be sufficient to produce the variability required given that matched controls are involved. If not, this pilot study will provide the data to carry out a sample-size calculation for a future larger clinical study. The analysis of data from this study will be primarily focused on descriptive statistics and estimates of precision to inform a planned larger validation study. The proposed sample size in our study is also consistent with the findings from a study on the target sample sizes set for pilot and feasibility randomized controlled trials in the United Kingdom [28].

For the HPLC/MS metabolite measurement, assuming a coefficient of variance of 30%, which corresponds to several multiples of observed technical variation, power calculations indicate this study will be 80% powered to detect changes of 27%. The minimum detectable effect size was calculated using G*Power [29,30].

